### Sample Size

In this study, the sample size was calculated based on the difference in the change in SCORAD score from baseline (week 0) to week 4, as the primary indicator, between the treatment group (urea ointment and WSZY pills) and control group (urea ointment and placebo WSZY pills). Based on previous evidence on the efficacy of TCM for AD treatment, we used a difference of 9.8 (SD 12) points [16]. ‌Sample size estimation‌ was performed using PASS 15.0 software (NCSS Statistical Software). Using the SD of 12.0, the sample size calculation for the 2:1 randomization design indicated that 36 patients with AD in the treatment group and 18 patients with AD in the control group would provide 80% statistical power to detect a difference of 9.8 points in the improvement in the SCORAD score at a 2-tailed α level of .05. Considering a dropout rate of 10%, we plan to enroll 40 patients with AD and 20 patients with AD in the treatment group and control group, respectively.

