### Outcomes

#### Primary Outcome

The primary outcome indicator in this study is the difference in the SCORAD score change from baseline (week 0) to week 4. The SCORAD index is made of the affected body surface area, skin lesion severity, and patient self-assessment of itching and quality of sleep. It is an evaluation method to assess the severity of AD as objectively as possible.

The SCORAD score includes the doctor's assessment (A, B) and the patient's own assessment (C), which is the most comprehensive evaluation method. (A) involves evaluating the affected area, including the head and neck area (accounting for 9%), both upper limbs (accounting for 9% each), both lower limbs (accounting for 18% each), the front and back of the trunk (accounting for 18% each), and the genital area (accounting for 1%). (B) involves 6 clinical features, including erythema, edema or papules, exudation or scabbing, epidermal peeling, lichenification, and dryness. Each feature is scored according to its severity, ranging from 0 to 3 points for each item. The patient self-assessment (C) includes itching and sleep deprivation in the last 3 days. The SCORAD score is calculated as A/5+7×B/2+C, with the total score ranging from 0 to 103 points. A higher score indicates a more severe disease condition. According to the score, the condition is considered mild (0-24 points), moderate (25-50 points), or severe (>50 points) [17]. In this study, the SCORAD will be estimated at baseline (week 0), week 2, week 4, and week 8.

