### Statistical Analysis

All data will be systematically recorded in the CRF and subsequently entered into a dual-validated electronic database using EpiData software 3.1, with final analyses performed using SAS 9.4. Quantitative variables that are normally distributed will be described using mean and SD, and those a skewed distribution will be described using median and interquartile range. Student *t* tests or Wilcoxon rank-sum tests will be used to compare the differences between groups for quantitative variables as appropriate, depending on the data distribution. Categorical variables will be presented as frequencies and proportions (%), and chi-square tests will be used to compare the differences in categorical variables between the groups. In addition, when the expected frequency is low (<1), Fisher exact tests will be used to compare the differences in categorical variables between the groups. In this study, a 2-tailed α level of .05 will be viewed as statistically significant. Statistical analyses will follow the intention-to-treat principle, including all randomly assigned patients regardless of protocol adherence or study completion [21]. We will handle missing data based on the assumption of missing-at-random and use the sequential regression multiple imputation method, which imputes missing values using regression models for each variable, conditional on the other variables in the data [22]. Additionally, analyses will be performed on both the full analysis set and the per-protocol set.

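### The primary test is chosen from the data while outcomes are multiply imputed, so the test and its target are not fixed in advance and can differ between imputed data sets

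*Protocol article*

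**What the plan says.** All the rules at issue stand in the Statistical Analysis section of the protocol article.

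- **Quantitative outcomes:** the t test is one option, and the rule for the alternative reads: "Wilcoxon rank-sum tests will be used to compare the differences between groups for quantitative variables as appropriate, depending on the data distribution". The criterion is not given, nor whether it is applied once or in each completed data set.
- **Categorical outcomes:** "chi-square tests will be used to compare the differences in categorical variables between the groups", with a second data-dependent switch: "when the expected frequency is low (<1), Fisher exact tests will be used".
- **Missing data:** the plan is to "use the sequential regression multiple imputation method" under missing at random.
- **Population:** intention to treat, "including all randomly assigned patients regardless of protocol adherence or study completion", so imputed values enter the tests.

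The Primary Outcome section defines the endpoint as "the difference in the SCORAD score change from baseline (week 0) to week 4" and sets no separate test for it, so it falls under the general rule. In the Sample Size section the planning value is a mean difference: "we used a difference of 9.8 (SD 12) points".

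**The concern.** With complete data, a rule that picks t or Wilcoxon from the distribution already leaves the primary test open until the data are seen. The two tests also have different targets: a difference in mean change, or a rank-based comparison of the two distributions.

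Multiple imputation sharpens this. There is no longer one distribution to inspect but several completed data sets. A check made in each may favour the t test in some and Wilcoxon in others, and results with different targets cannot be averaged into one answer. Standard pooling also needs an estimate and a standard error from every set, which a bare Wilcoxon or Fisher p value does not supply.

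At stake is whether the main result is one pre-stated quantity, matched to the sample size, or one settled at analysis. The same applies to rescue use and recurrence.

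**Working it through.** **1. Target implied by the sample size.** Inputs from the Sample Size section: difference 9.8, SD 12, 2:1 allocation, two-sided alpha .05, power 80%, dropout 10%.

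Control n = (1.960 + 0.842)² × 12² × (1 + 1/2) / 9.8² = 7.85 × 144 × 1.5 / 96.04 ≈ 17.7, so 18 control and 36 treatment. Power at 18/36 is 80.8% (normal formula) or 79.3% (noncentral t). Dropout: 18/0.9 = 20 and 36/0.9 = 40. The stated figures are reproduced, and they belong to a comparison of means.

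**2. How often imputed sets would call for different tests.** Assumptions, none of them in the protocol: Shapiro-Wilk at .05 in each arm, applied in each of 20 imputed sets; regression imputation; effect 9.8, SD 12; 40 and 20 patients. Share of simulated trials with a mixed choice at 10% missing (6 of 60), from runs with somewhat different settings:

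| Run | Normal | Skewness 0.5 | Skewness 1 |
|---|---|---|---|
| 800 trials per column | 28% | 43% | 51% |
| Separate repeat | 32% | 41% | 52% |

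A further run (400 trials per cell, moderately skewed gamma errors) gave 32% for normal and 43% for skewed data. With 5% missing it gave 16% and 34%; with 20% missing, 43% and 59%.

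**3. Does the switch change the significance verdict?** Share of trials in which the 20 sets fall on both sides of p = .05, at skewness 0 / 0.5 / 1:

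| Run | With the switch | t test only |
|---|---|---|
| Repeat run | 25 / 28 / 23% | 24 / 26 / 21% |
| 500 trials per skewness, assumed correlations 0.6 and 0.3 | 28 / 25 / 26% | 27 / 24 / 25% |

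The switch adds 1 to 2 percentage points. When the median p value over the sets is compared with .05, switched and t-only analyses disagree in 1.2%, 1.6% and 5.2% of trials in the 500-trial run, and in about 0-5% in the repeat.

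**4. The Fisher switch.** With 20 of 60 patients in the control arm, the expected control events are total events × 20/60. Two events give 0.67 (Fisher); three give 1.00 (chi-square). One imputed event can change the test.

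**5. Can a pre-stated analysis be pooled at this size?** Simulated type I error at nominal .05 (2,000 null trials, 10% missing, 20 imputations):

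- mean difference, Rubin's rules: 0.051
- Mann-Whitney probability with its SE, Rubin's rules: 0.056
- risk difference, Rubin's rules: 0.054
- chi-square, D2 rule: 0.043

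Monte Carlo error is about √(0.05 × 0.95/2000) = 0.005, so all four are close to nominal.

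**The case against.** **Pooling is possible.** A reader might infer that these tests cannot be pooled at all. That is not so. The t-test mean difference is the standard case for Rubin's rules, and chi-square and rank comparisons have established routes, which behaved well in step 5. What stands is narrower: the raw Wilcoxon or Fisher p value is not directly poolable, and the protocol names none of the substitutes.

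**Conflict is not certain.** The document does not say that the distribution is checked in each imputed set. If it is judged once, for example on observed or blinded data, the sets cannot disagree. The 30-50% therefore describes one assumed way of applying the rule. Judging once still leaves the test and its target to be chosen after data are seen.

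**Split p values are not caused by the switch.** A reader might take the 22-29% of trials whose sets straddle p = .05 as the share in which the switch decides significance. Step 3 shows almost the same share with the t test alone. It is ordinary between-imputation variation, which pooling absorbs and which would remain under the fix.

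**Some of this is SAP detail.** The number of imputations, the pooling formula and the normality criterion are commonly left to a fuller document, and their absence is no finding. The point rests on what the article does state: a data-driven test alongside multiple imputation.

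**The target is already indicated.** The sample size does point to a mean difference. That supports fixing the primary analysis there; it does not cancel a rule that permits another test.

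**Conclusion.** The point holds in a limited form. As written, the primary test and its target are not fixed in advance, can depart from the mean difference that sizes the trial, and can differ between imputed sets if the check is repeated in each one. The last occurs in about 30-50% of simulated trials at the planned 10% missing, under the assumed Shapiro-Wilk check and 20 imputations. The share rises with more missing data, which the protocol's own Limitations section treats as possible.

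The expected effect on the significance verdict is small, roughly 0-5% of simulated trials. The documents do not support saying that the planned analysis is unpoolable or that the switch would often reverse the conclusion. The weakness is in pre-specification and in having one clear estimate to report. It should be corrected because the correction is cheap.

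**What to change.** Before unblinding, name one analysis per outcome, identical in every imputed data set, with no normality gate:

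- SCORAD change to week 4 (primary) and the other quantitative scales: between-group difference in means with its standard error.
- Rescue use and recurrence: risk difference with its standard error.

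Pool each by Rubin's rules and report it with a 95% CI. Keep Wilcoxon, chi-square and Fisher tests as supportive analyses of observed data.

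The cost is analysis wording only; no new data or patients are needed. The small downside is that, for strongly skewed secondary outcomes, a mean difference is less efficient than a rank test, which stays available as the supportive analysis.

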### Safety Assessment

Prior to enrollment in this study, all patients diagnosed with mild-to-moderate AD will receive a comprehensive risk disclosure through a standardized informed consent process. Adverse events are defined as any adverse medical occurrences following administration of the treatment, encompassing symptoms, physical signs, diagnosable diseases, or laboratory abnormalities, regardless of causality assessment. Participants will be required to report all adverse events occurring during the 4-week treatment period and the subsequent 4-week follow-up. All reported events will be systematically documented in the CRF with precise temporal and descriptive details. In accordance with clinical practice guidelines, any participant experiencing a severe adverse event will undergo immediate study discontinuation and receive protocol-specified medical management at no cost to the participant. This safety protocol ensures both rigorous data collection and participant welfare throughout the trial duration. Given that this trial presents minimal risks, we will not establish a data monitoring committee.

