### Objectives

In this study, we plan to implement a double-blind, randomized, placebo-controlled clinical trial to evaluate the efficacy of WSZY pills for mild-to-moderate AD. Our primary objective is to evaluate the effect of WSZY pills on the severity of AD and recurrence rates in patients with mild-to-moderate AD. The secondary objectives are to assess the effect of WSZY pills on itching level, quality of life, and safety in patients with mild-to-moderate AD. This trial will provide additional evidence for the clinical efficacy of WSZY pills for AD treatment, which may provide a new treatment option for patients with mild-to-moderate AD. We hypothesized that WSZY pills can effectively alleviate the disease condition of patients with mild-to-moderate AD.

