### Interventions

In this study, patients with AD in the treatment group will receive 3 sessions of urea ointment and 7.5 g of WSZY pills each day for 4 weeks. To ensure the correct application of urea ointment, we will instruct the patients to apply urea ointment to the affected area and instruct patients that one knuckle length of urea ointment should be used to cover no more than 1% of the body surface area. This should be followed by a finger massage of the area for 3 minutes to 5 minutes to promote absorption. To ensure the correct administration of WSZY pills, we will instruct patients to take 1 bag (2.5 g) of the WSZY pills per dose, 3 times a day with water.

Patients with AD in the control group will also receive 3 sessions of urea ointment and 7.5 g of placebo WSZY pills each day for 4 weeks. The placebo WSZY pills are made of dextrin and are produced and provided by the same company, which maintains complete consistency with the WSZY pills in terms of appearance, weight, color, odor, and package. The application, individual guidance, and instruction for placebo WSZY pill administration among patients in the control group is completely in line with that in the treatment group.

In this study, patients will be instructed not to use any additional treatment for AD. If a patient uses additional treatment for an emergency condition, detailed information should be recorded, and the patient should be withdrawn.

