## Results

The study received ethics permission in September 2024, and trial registration was completed in October 2024. Recruitment started in December 2024 and is expected to be completed by December 2025. As of June 2025, 30 participants with mild-to-moderate AD were enrolled. Data analysis will begin in January 2026. The main results of the trial are expected to be submitted for publication in peer-reviewed scientific journals in the summer of 2026.

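### The emergency-treatment and severe-adverse-event rules do not separate stopping study drug from leaving the study, so followed as written they end the remaining assessments

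*Protocol article*

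**What the plan says.** Two rules in the Protocol article remove a patient after an event.

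- **Interventions**, on additional treatment: "If a patient uses additional treatment for an emergency condition, detailed information should be recorded, and the patient should be withdrawn". The text does not say whether the patient is withdrawn from study drug or from the trial.
- **Safety Assessment**, on severe events: "any participant experiencing a severe adverse event will undergo immediate study discontinuation". The patient also receives medical management.

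Other text bears on how these rules should be read.

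- Safety Assessment also states: "Participants will be required to report all adverse events occurring during the 4-week treatment period and the subsequent 4-week follow-up". It does not say whether this covers patients already discontinued.
- Table 1 (Secondary Outcomes) schedules SCORAD at weeks 0, 2, 4 and 8. Routine blood and urine tests, biochemistry and ECG are at baseline and week 4 only. Recurrence is assessed at week 8 only.
- Statistical Analysis applies intention-to-treat to every randomised patient. On gaps it says: "We will handle missing data based on the assumption of missing-at-random", using sequential regression multiple imputation.
- Objectives: "The secondary objectives are to assess the effect of WSZY pills on itching level, quality of life, and safety". Recurrence is part of the primary objective.
- On oversight, Safety Assessment says: "Given that this trial presents minimal risks, we will not establish a data monitoring committee".

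**The concern.** Stopping a drug and leaving a trial are different decisions. The first protects the patient. The second also ends data collection. Both rules use words that on their face describe the second, and no section brings them back to the first.

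The Interventions rule is the firmer part. A patient whose dermatitis flares and who takes another treatment in an emergency is to be withdrawn, and such a patient is informative about whether the pills work. The Discussion describes levocetirizine as planned remedial treatment for severe itching, so the rule is best read as covering other treatments.

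For severe events, the later course of the affected patient belongs in the trial record, because safety is a stated objective and no monitoring committee will look at it separately. For either rule, an event before week 4 means the primary outcome for that patient is imputed when it could have been observed.

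**Working it through.** **1. What each rule removes if followed as written (Table 1)**

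| Timing of event | Assessments not made |
|---|---|
| Before week 4 | Week-4 SCORAD (primary outcome); the only scheduled post-baseline blood, urine and biochemistry tests and ECG; all week-8 assessments; the week-2 visit too if the event comes before it |
| Between weeks 4 and 8 | Week-8 SCORAD, recurrence and adverse-event assessments |

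Nothing suggests that data collected before the event are discarded.

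**2. The plan's own sample size**

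Inputs from Sample Size: difference 9.8, SD 12, two-sided alpha .05, allocation 2:1, "36 patients with AD in the treatment group and 18 patients with AD in the control group", 10% dropout.

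- Standard error = 12 × √(1/36 + 1/18) = 3.464.
- Standardised difference = 9.8 / 3.464 = 2.829.
- Normal approximation: power = Φ(2.829 − 1.960) = 80.8%.
- Noncentral t with 52 degrees of freedom: power = 79.3%.
- Dropout: 36/0.9 = 40 and 18/0.9 = 20.

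The stated 36/18 and 40/20 reproduce. The dropout allowance is (40 + 20) − (36 + 18) = 6 patients.

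**3. How many patients might be affected**

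The documents give no severe-event rate and no rate of withdrawal for additional treatment. For severe events I assume a range p. The expected number is 60p, and the chance of at least one is 1 − (1 − p)^60.

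| Assumed p | Expected among 60 | Chance of at least one |
|---|---|---|
| 0.5% | 0.3 | 26.0% |
| 1% | 0.6 | 45.3% |
| 2% | 1.2 | 70.2% |
| 5% | 3.0 | 95.4% |

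No figure is available for the Interventions rule, so these counts do not cover it.

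**4. Effect on power if losses come on top of the planned dropout (noncentral t)**

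| Evaluable (treatment/control) | Power | Change from 36/18, percentage points |
|---|---|---|
| 36/18 | 79.3% | none |
| 35/18 | 78.9% | −0.4 |
| 36/17 | 77.7% | −1.6 |
| 34/17 | 76.9% | −2.4 |

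If the affected patients fall within the allowance of 6, there is no further loss.

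**5. Imputation**

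The affected patients stay in the analysis set with imputed scores. Missing at random requires that, given the recorded data, withdrawal does not depend on the unseen score. A flare between visits that leads to emergency treatment and then withdrawal may breach this, because the visits already recorded need not show it. Whether it would do so here cannot be determined from the documents.

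**The case against.** The best case on the other side has four parts.

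- **Study discontinuation may simply mean stopping study treatment.** The same section asks for adverse-event reporting through follow-up, provides medical management after the event, and says the safety procedures secure rigorous data collection throughout the trial. Study Design says all participants have the 4-week follow-up. This stands in part: it makes some continued contact likely after a severe event. It does not say that the SCORAD visits, laboratory tests or ECG continue, and it does nothing for the Interventions rule.
- **The article condenses a full protocol (version 1.0) that is not shown.** Post-discontinuation procedures are commonly left to such a document. That would answer a complaint about missing detail. Here the article states two rules whose wording points to leaving the trial. If the full protocol is clear, the article's wording should be aligned with it.
- **Missing at random need not fail.** The event is recorded, and imputation conditions on other variables. This stands: failure is possible but not shown. Observed visits would make the assumption unnecessary for these patients.
- **The numbers are small.** This stands and limits the priority.

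A reader might also infer that withdrawal contradicts the intention-to-treat commitment. It does not: that commitment covers patients who do not complete, and imputation keeps them in. Nor do the documents support saying that safety follow-up certainly ends after a severe event, or that the trial becomes underpowered.

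**Conclusion.** The point holds as a defect of wording with a modest practical cost. It is firmer for the emergency-treatment rule than for the severe-event rule, which matters only if study discontinuation means leaving the study.

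The cost lies in observations lost from a few informative patients: an imputed primary outcome and no scheduled post-baseline laboratory tests or ECG for events before week 4, and no week-8 SCORAD or recurrence assessment for later ones. The effect on power is negligible, at most 2.4 percentage points in the cases examined and none within the dropout allowance. The patient counts rest on an assumed severe-event rate of 0.5% to 5%, and the number withdrawn for additional treatment is unknown. Priority is low to moderate.

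**What to change.** **Interventions:** replace the withdrawal instruction with a statement that a patient who uses additional emergency treatment stops study drug, has that treatment recorded, and continues the remaining scheduled visits.

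**Safety Assessment:** state that a severe adverse event leads to immediate discontinuation of study drug.

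**In both places:** add that the remaining Table 1 visits, the week-4 laboratory tests and ECG, and adverse-event follow-up continue to week 8 unless the patient withdraws consent. If the full protocol already says this, bring the article into line with it.

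**Cost:** about one sentence in each of two sections, by amendment, using visits and tests already scheduled. The Results section reports "As of June 2025, 30 participants with mild-to-moderate AD were enrolled", so at that date 60 − 30 = 30 patients could still be enrolled under the clarified rule. The downside is a few visits by patients who are off treatment. Scores after additional treatment will also partly reflect that treatment, which is why it must be recorded.
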